**1.6 Sample Size Calculation**

The sample size is calculated to compare overall survival (OS) between two arms. The sample size was estimated on the basis of the overall survival (OS) of 14.9 mon in the combined group and 8.2 mon in the FOLFOX4 only group, which were obtained from the data of our retrospective cohort of patients. The minimum sample size was 106 for the two groups (two-sided α= 0.05; β = 0.20; power, 80%;10% of patients were added to compensate for any loss to follow-up).

**2. Analysis sets**

**2.1 Definitions**

The full analysis set comprises all subjects who were so called treatment candidates irrespective of the actually received treatment.

The per-protocol analysis set comprises the same treatment candidates, with the exclusion of those who were not treated by ATRA-FOLFOX4.

The safety analysis set: The safety analysis set is the same as the intention-to-treat analysis set without estimates for missing values.

Missing values that are assumed to be missings at random (MAR) or missings completely at random (MCAR) are estimated using multiple imputation methods for all analysis sets except analysis set.

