**9.2 Populations for Analysis**

Intent-to-treat (ITT) population: any patients assigned to a treatment group by the randomization process, regardless of whether patients received any study treatment or received a different study treatment from which they were randomized. This is the primary data set for the test of overall survival, analyses of secondary efficacy endpoints like TTP, symptom assessment and baseline characteristics.

Per protocol (PP) population: all randomized subjects except for subjects who 1) have wrong diagnosis of cancer; 2) are not treated; 3) are not treated with the study therapy as assigned by the randomization. This is the primary dataset for the test of overall survival.

Safety population: All subjects who received at least one dose of study medications. This is the primary data set for dosing, safety, concomitant medications.

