**1.4 Study design**

This is a multicenter, double-blinded, placebo-controlled, randomized clinical trial in advanced HCC patients with EHM. The randomization schedule was generated by an independent statistician using randomization block method in SAS 9.4. Eligible subjects enrolled in the study all received a unique subject identification number and were randomly assigned to a treatment group ATRA- FOLFOX4 or FOLFOX4 alone in a ratio of 1:1 (Website: http://pro32.irtone.com/). Both subjects and investigators did not know the true treatments and were blinded until emergency un-blinding and after database lock. Our study has been registered at <http://www.chictr.org.cn> (ID: ChiCTR-IIR-17012916).

After screening for eligibility and signing of informed consent, qualified subjects will be randomized in a 1:1 ratio to receive ATRA+FOLFOX4 (Group A) or Placebo + FOLFOX4 (Group B). Randomization will be stratified by site and treatment assignments will remain blinded throughout the study.

Names of Therapeutic Agents:

- All-trans-Retinoic Acid (ATRA)
- Oxaliplatin (OXA)
- 5-Fluorouracil (5FU)
- Leucovorin (LV)

Mode of Administration:

ATRA+FOLFOX4 (Group A): ATRA 20 mg oral 3 times/day for 3 days prior to the initiation of chemo (FOLFOX4). ATRA will be discontinued at the end of FOLFOX4(OXA 85mg/m2 iv day1, LV 200mg/m2 iv day1 and day 2, 5FU 400mg/m2 iv bolus at hour 2 and then 600 mg/m2 iv over 22 hours on day 1 and day 2, once every 2 weeks) and a total of 6 cycles were performed. Placebo+FOLFOX4 (Group B):The placebo (replacing ATRA) will be given orally 3 times/day for 3 days prior to the chemo. The placebo will then be discontinued at the end of FOLFOX4 and a total of 6 cycles were performed. The follow-up phase began once a patient terminated the treatment phase.

A more detailed description of the in- and exclusion criteria can be found in the in- and exclusion criteria below.

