**2.2 Application**

Analyses in the full analysis set: The intention-to-treat analysis, any patients assigned to a treatment group by the randomization process, regardless of whether patients received any study treatment or received a different study treatment from which they were randomized. This is the primary data set for the test of overall survival, analyses of secondary efficacy endpoints like TTP, symptom assessment and baseline characteristics.

Analyses in per-protocol analysis set: The per-protocol analysis, all randomized subjects except for subjects who 1) have wrong diagnosis of cancer; 2) are not treated; 3) are not treated with the study therapy as assigned by the randomization. This is the primary dataset for the test of overall survival.

Analyses in safety analysis set: All subjects who received at least one dose of study medications. This is the primary data set for dosing, safety, concomitant medications.

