**5.1 Primary analyses**

OS will be compared between two treatment groups, using a log-rank test procedure at 5% significance level and the survival curves will be estimated using Kaplan-Meier estimates. Additional analyses of survival will include the computation of hazard ratios (HRs) and the estimation of survival functions. The survival hazard ratio of TARA+FOLFOX to placebo + FOLFOX and an associated two-sided 95.0% confidence interval will be computed using unadjusted and adjusted Cox proportional hazards modeling. Cox models will include treatment stratified by the above-mentioned stratification factors, and an adjusted model which will include a pre-defined list of covariates as well as the above-mentioned stratification factors, all as covariates. This analysis is executed based according to the intention-to-treat principle (ITT).

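### SAP 2.1 defines a per-protocol set with no control arm, and both the ITT and the per-protocol set are named primary for overall survival

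*Combined protocol and SAP*

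**What the plan says.** **Per-protocol set.** SAP 2.1 reads: "The per-protocol analysis set comprises the same treatment candidates, with the exclusion of those who were not treated by ATRA-FOLFOX4". SAP 1.4 uses that treatment name for one arm only; the other arm receives placebo with FOLFOX4. SAP 2.2 and protocol 9.2 define the set differently. They remove randomised patients with a wrong cancer diagnosis, those not treated, and those not given their assigned therapy, whichever arm they are in.

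**Primary set for OS.** On the ITT set, SAP 2.2 says: "This is the primary data set for the test of overall survival". Its next paragraph, on the per-protocol set, ends: "3) are not treated with the study therapy as assigned by the randomization. This is the primary dataset for the test of overall survival". Protocol 9.2 contains the same pair of statements; on ITT it says "This is the primary data set for the test of overall survival, analyses of secondary efficacy endpoints". SAP 5.1 places the primary OS analysis under the intention-to-treat principle. Protocol 9.3, which specifies the log-rank test at 5%, names no analysis set.

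**Full analysis set.** SAP 2.1 says: "The full analysis set comprises all subjects who were so called treatment candidates irrespective of the actually received treatment". SAP 1.5 defines treatment candidates as patients with the listed eligibility characteristics. SAP 2.2 describes the analysis in that set as covering any patient assigned to a group by randomisation.

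**The concern.** An analysis plan should allow two statisticians working separately to build the same datasets and run the same confirmatory test. Here they could not.

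- An analyst who builds the per-protocol set from the section headed Definitions gets a single-arm dataset, from which no log-rank test or hazard ratio can be computed.
- An analyst looking for the primary OS population finds two, and one of them rests on exclusions made after randomisation. If the two results disagree, each has text in both the protocol and the SAP to support calling it primary.
- The ITT set is not firmly defined either. Read with SAP 1.5, the full analysis set in SAP 2.1 would allow a randomised patient later found ineligible to be dropped.

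OS is the only primary endpoint, so what is left open is the population for the trial's one confirmatory claim.

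**Working it through.** **1. The plan's own figure.** Inputs from SAP 1.6 and protocol 9.1: OS of 14.9 and 8.2 months (read as medians), two-sided alpha 0.05, power 80%, 10% added for loss, minimum total 106. SAP 1.4 gives 1:1 allocation.

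- Hazard ratio with exponential survival: 8.2/14.9 = 0.550.
- (1.960 + 0.842)² = 7.849.
- Freedman events: 7.849 × [(1 + 0.550)/(1 − 0.550)]² = 93.3, rounded up to 94. Allowing for loss, 94/0.9 gives 105 and 94 × 1.1 gives 104.
- Schoenfeld events: 4 × 7.849/(ln 0.550)² = 88.02, rounded up to 89, then 99 or 98 after loss.

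The Freedman route comes within two patients of 106, if the 94 events are taken as 94 patients. The point below does not depend on a sample size error.

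**2. What each per-protocol wording leaves.** At 1:1, 106/2 = 53 patients per arm.

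| Source | Who is removed | ATRA arm left | Placebo arm left |
|---|---|---|---|
| SAP 2.1, literal | anyone not treated with ATRA-FOLFOX4 | up to 53 | 0 |
| SAP 2.2 and protocol 9.2 | wrong diagnosis, untreated, not treated as assigned | up to 53 | up to 53 |

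The zero assumes that no placebo patient received ATRA by mistake. Any who did would not be valid controls.

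**3. Which set is primary for OS.**

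| Place | ITT | Per-protocol |
|---|---|---|
| Protocol 9.2 | named primary | named primary |
| Protocol 9.3 | no set named | no set named |
| SAP 2.2 | named primary | named primary |
| SAP 5.1 | named | not mentioned |

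The text available gives no order of testing and no division of alpha between the two sets.

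**4. Type I error if success on either set counted.** Let Z₁ be the ITT log-rank statistic and Z₂ the per-protocol one, and let f be the share of patients (and so of events) excluded from per-protocol. With exclusion at random, the correlation is √(1 − f) and

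alpha = 1 − P(|Z₁| ≤ 1.96 and |Z₂| ≤ 1.96), bivariate normal.

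The documents give no value for f, so a range is shown.

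| f | correlation | alpha |
|---|---|---|
| 1% | 0.995 | 0.055 |
| 2% | 0.990 | 0.057 |
| 5% | 0.975 | 0.060 |
| 10% | 0.949 | 0.065 |
| 15% | 0.922 | 0.068 |
| 20% | 0.894 | 0.071 |

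Two independent tests would give 1 − 0.95² = 0.0975, but these two tests share most of their patients.

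**5. Full analysis set.** SAP 2.1 with SAP 1.5 gives patients who meet the eligibility criteria; SAP 2.2 gives everyone randomised. The two coincide unless a randomised patient is later found ineligible, and no rule covers that case.

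**The case against.** The strongest reply is that the documents already contain the right answers. SAP 2.2 and protocol 9.2 agree on a workable per-protocol definition, so the sentence in SAP 2.1 is very probably a drafting slip that nobody would carry out. SAP 5.1, the section that specifies the confirmatory test, says ITT, and SAP 5.2 does the same for the secondary outcomes. None of the analysis sections available calls for a per-protocol analysis. No rule says that success on either set is enough, and the exclusion shares are assumed. The per-protocol exclusions are narrow, the study population is pathologically confirmed and allocation is blinded, so 1% to 2% excluded (alpha 0.055 to 0.057) is at least as plausible as 10% to 20%. On the full analysis set, SAP 1.4 says that qualified subjects are randomised, and SAP 2.2 treats the set as ITT.

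Much of this stands. The intent can be inferred, the inflation is conditional and modest, and the full analysis set conflict bites only when an eligibility error comes to light. But SAP 5.1 does not cancel the per-protocol label in SAP 2.2 or in protocol 9.2, nothing says which section governs, and the protocol read alone cannot settle the matter. Inferred intent is weak protection once results can be seen.

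**Conclusion.** The concern holds and should be fixed. As written, SAP 2.1 gives a per-protocol set without a comparator: 53 of 53 planned placebo patients excluded, taking the stated minimum of 106 at 1:1. Protocol 9.2 and SAP 2.2 each name two primary datasets for OS, and SAP 5.1 supports only one of them. The full analysis set has two definitions that part company for randomised patients later found ineligible.

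The cost in type I error is conditional: about 6.0% to 7.1% for 5% to 20% excluded, and about 5.5% to 5.7% for 1% to 2%. It assumes that either result could be claimed, that exclusion is random, and that the correlation equals the square root of the share kept. Bias is the larger risk, because leaving out untreated or wrongly treated patients is selection after randomisation; the documents give no figures from which to size it. The SAP text between sections 2.2 and 4 was not in the copy reviewed, so a rule placed there could not be checked.

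**What to change.** - **SAP 2.1, full analysis set:** all randomised patients, analysed in the arm to which they were randomised. Remove the reference to treatment candidates.
- **SAP 2.1, per-protocol set:** randomised patients with confirmed HCC who received the treatment assigned to them, whether ATRA plus FOLFOX4 or placebo plus FOLFOX4. This brings it into line with SAP 2.2 and protocol 9.2.
- **Protocol 9.2 and SAP 2.2:** delete the sentence naming the per-protocol set as primary for OS, and call that analysis a sensitivity analysis.
- **Protocol 9.3 and SAP 5.1:** state that the single confirmatory OS test is the log-rank test in all randomised patients.

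The cost is a few sentences and no new data. The change follows the choice already made in SAP 5.1.

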**2.2 Application**

Analyses in the full analysis set: The intention-to-treat analysis, any patients assigned to a treatment group by the randomization process, regardless of whether patients received any study treatment or received a different study treatment from which they were randomized. This is the primary data set for the test of overall survival, analyses of secondary efficacy endpoints like TTP, symptom assessment and baseline characteristics.

Analyses in per-protocol analysis set: The per-protocol analysis, all randomized subjects except for subjects who 1) have wrong diagnosis of cancer; 2) are not treated; 3) are not treated with the study therapy as assigned by the randomization. This is the primary dataset for the test of overall survival.

Analyses in safety analysis set: All subjects who received at least one dose of study medications. This is the primary data set for dosing, safety, concomitant medications.

**4. Analysis variables**

**4.1 Primary outcome**

Overall Survival (OS): OS is defined as the time from randomization to the time of death from any cause. Subjects who are alive at the time of the final analysis or who have become lost to follow-up will be censored at their last known alive date.

**4.2 Secondary outcome**

Progression Free Survival (PFS): PFS is defined as the time (in months) from randomization to the time of radiographic disease progression. Subjects without progression will be censored at their last tumor assessment date. Subjects who have no on-study tumor assessments will be censored at the date of randomization.

Objective Response Rate (ORR): ORR is defined as the proportion of randomized subjects in each treatment arm whose best response is a CR or PR using the modified RECIST for HCC.

Disease Control Rate (DCR): DCR is defined as the proportion of randomized subjects in each treatment arm whose best response is a CR, PR or SD using the modified RECIST for HCC.

**4.3 Safety Outcomes**

Study drug toxicities will be assessed continuously, which include vital sign, physical exam, neurological exam, EKG, Echo, clinical lab tests (hemoglobin, hematocrit, red blood cell, total leukocyte count with differential, platelet count, AST, ALT, total bilirubin, direct bilirubin, alkaline phosphatase, lactate dehydrogenase (LDH), creatinine, BUN or urea, blood glucose, total protein, albumin, sodium, potassium, chloride, total calcium, phosphorus, magnesium, ammonia, and AFP) and specialty exams (chest X-ray, CT, MRI, Bone Scan, etc.). All the adverse events will be evaluated according to the NCI CTCAE (Version 4.0), on a continuous basis while the subject is on study. Scheduled evaluations will occur every 4 weeks.

**5. Statistical analyses**

For all analyses (including analysis of primary outcome) appropriate descriptive statistics (mean, standard deviation, median, interquartile range, percentages) depending on the scale and distribution of the outcome variable are presented by treatment group. Standardized mean differences are provided where possible in order to provide insights into the magnitude of differences between the treatment groups.

**5.1 Primary analyses**

OS will be compared between two treatment groups, using a log-rank test procedure at 5% significance level and the survival curves will be estimated using Kaplan-Meier estimates. Additional analyses of survival will include the computation of hazard ratios (HRs) and the estimation of survival functions. The survival hazard ratio of TARA+FOLFOX to placebo + FOLFOX and an associated two-sided 95.0% confidence interval will be computed using unadjusted and adjusted Cox proportional hazards modeling. Cox models will include treatment stratified by the above-mentioned stratification factors, and an adjusted model which will include a pre-defined list of covariates as well as the above-mentioned stratification factors, all as covariates. This analysis is executed based according to the intention-to-treat principle (ITT).

**5.2 Secondary analyses**

The secondary outcomes as mentioned under 4.2 are analyzed as follows:

PFS will be compared between two treatment groups, using a log-rank test procedure at 5% significance level and the survival curves will be estimated using Kaplan-Meier estimates. This analysis is executed based according to the intention-to-treat principle (ITT).

The efficiency (ORR and DCR) will be compared between two treatments using Chi-Square Test or Fisher’s Exact Test. Repeated measures ANOVA (if applicable) will be used or two-group t-test/Wilcoxon signed rank test on difference between baseline score. This analysis is executed based according to the intention-to-treat principle (ITT).

**5.3 Safety Analyses**

We report absolute frequencies of events as well as percentages per group separately by safety measure without imputed values for missing in the full analysis set.
